**Fig. 1 Fig1:**
[figure not shown]
Study flow chart. Abbreviations: *eGFR* estimated Glomerular Filtration Rate, *HRQoL* Health-Related Quality of Life, *NGA* NephroGeriatric Assessment

DIALOGICA is aimed to run for a total of 4 years with a minimum follow-up of 1 year in the second stage. The study is conducted according to the principles of the Declaration of Helsinki and the ICH-GCP guidelines. Primary ethical approval was obtained from the medical research ethics committee of the The Hague region (METC Zuidwest Holland) on May 24th 2019 (reference number 19–071). Local medical research ethics committees in participating centres will also be asked for local ethical approval. The study is registered in the Netherlands Trial Register under NL-8352.

### Study population

Inclusion criteria are age of 70 years and older and an eGFR between 10 and 15 mL/min/1.73m^2^ at the moment of inclusion. Due to the nature of the assessments that will be performed in this study (described in detail later), illiterate patients and those unable to speak Dutch will be excluded. All patients have to provide written informed consent. When a patient appears to have severe cognitive impairment, a geriatrician will judge if a patient is mentally competent to provide the required consent.

### Data registration

At baseline, all relevant demographical and clinical data will be collected. In the first stage of the study, a follow-up visit will be scheduled once-yearly until the start of the second stage. In the second stage, data collection will be performed at start, after 3 months, 6 months, 12 months, and thereafter annually until end of follow-up or end of the study. All data will be recorded in a database developed in collaboration with Nefrovisie. Nefrovisie is the Dutch Quality Institute for Nephrology which hosts the Renine-database, in which all Dutch patients on kidney replacement therapy are registered. Upon consent, data for DIALOGICA will be linked to the Renine-database and the databases of three Dutch studies with similar or complementary study aims and outcomes: the *Dutch nOcturnal and hoME dialysis Study To Improve Clinical Outcomes* (DOMESTICO) study will compare HRQoL, clinical outcomes and costs in home dialysis patients with in-centre haemodialysis patients; the *Pathway for OLDer patients with End-stage Renal disease* (POLDER) project will assess the feasibility of implementing a geriatric assessment in routine predialysis care for older patients with an eGFR < 20 mL/min/1.73m^2^ and the *Optimizing Access Surgery In Senior haemodialysis patients* (OASIS) study will compare three strategies of vascular access in older patients using a randomised design [11–13]. The DIALOGICA database will be archived for future research during a minimum of 15 years after the completion of this study.

### Nephrogeriatric assessment

To assess the most common geriatric domains (i.e. functional, psychological, somatic, and social status) and the study’s outcome measures (i.e. HRQoL, clinical outcomes, and costs), a geriatric assessment tailored to the kidney failure population will be used. It is derived from the consensus-based test set used in a pilot study [11]. This nephrogeriatric assessment (NGA) consists of a combination of 12 questionnaires and seven tests and assessments (Table 1). Nine questionnaires are answered independently by the patient at home and three are conducted by an interviewer. All of the tests and assessments are performed in the participating centres. The NGA is performed at baseline and at a yearly interval during the first stage. Upon entering the second stage, a new NGA will be performed, repeated again at yearly intervals. The questionnaires on HRQoL, symptoms and costs are also repeated after 3 and 6 months into the second stage. To minimise inter-observer bias, the tests will be performed by trained geriatric or (pre) dialysis nurses only.

**Table 1 Tab1:** The nephrogeriatric assessment used in DIALOGICA

Domain	Measure	Type	Explanation	Scale / cut-off
Functional status	Activities of Daily Living (Katz) [14]	SAQ	Grading of dependency on 6 functions, e.g. bathing, dressing.	0–12, higher scores indicating more dependency, no cut-off values.
	Instrumental Activities of Daily Living (Lawton) [15]	SAQ	Grading of dependency on 8 more complex functions, e.g. handling finances, driving.	0–8 for women, 0–5 for men. Higher scores indicating more independency, no cut-off values.
	Fall risk assessment	IAQ	One-year history of falling and graded fear of falling.	Yes/no; 1 (‘no fear’) to 10 (‘very afraid’).
	Hand grip strength	T	Measured using a Jamar handheld dynamometer, 3 repetitive measurements for both hands.	Highest measurement is used for analysis. Individual cut-off values based on age and gender [16].
Psychological status	Montreal Cognitive Assessment (MoCA) [17]	T	Screening tool for cognitive impairment in 8 domains (visuospatial, naming, memory, attention, language, abstraction, delayed recall, orientation).	0–30, higher scores indicating better cognitive performance, < 26 indication of cognitive impairment.
	Six-item Cognitive Impairment Test (6-CIT) [18]	T	Fast, 6-item screening tool for dementia, assessing orientation, attention and memory.	0–28, higher scores indicating worse cognitive performance, > 10 indication of cognitive impairment.
	Letter-Digit Substitution Test (LDST) [19]	T	Speed-dependent task to measure speed of processing by matching letters to corresponding numbers provided in the key.	0–135 correct matches after 60 s, reference values based on age, gender and level of education [20].
	Geriatric Depression Scale (GDS-15) [21]	IAQ	Initial two-item screening tool (‘Whooley-questions’) on mood and anhedonia, if any of the 2 positive followed by 15 additional binary questions [22].	Yes/no, 0–15, higher scores indicating more or stronger degree of depressive symptoms, > 5 indicative of depression.
	Life Orientation Test - Revised (LOT-R) [23]	SAQ	10 Items including 4 filler items, 3 items for optimism and 3 items for pessimism. Scored using 5-point Likert scales.	0–12 per construct (optimism or pessimism) or 0–24 for total score (higher scores then indicating more optimism). Reference values based on age and gender [24].
Somatic status	Clinical Frailty Scale [25]	CA	Clinicians judgement of frailty based on 9 pictures with accompanying text.	1 (‘very fit’) to 9 (‘terminally ill’).
	Charlson Comorbidity Index [26]	CA	Comorbid conditions with weighted scores for the condition.	1–6 per condition, total range of 0–33. Higher scores indicating more or more severe comorbidity. No cut-off values.
	Surprise question	CA	Clinicians response to the question: “*Would I be surprised if the patient died in the next 12 months?*”, assessed by either nephrologist or (predialysis) nurse	Yes/no.
	Mini Nutritional Assessment - Short Form (MNA-SF) [27]	IAQ	6 Questions for assessing the risk of malnourishment.	0–7 ‘malnourished’, 8–11 ‘risk of malnourishment’, 12–14 ‘well-nourished’.
HRQoL and symptoms	Twelve-item Short Form Health Survey (SF-12) [28]	SAQ	12 Questions regarding HRQoL, resulting in a mental and physical component score. Scored using 3- and 5-point Likert scales. Used in Dutch nephrological care as PRO.	0–100, higher scores indicating better HRQoL, no cut-off values.
	Dialysis Symptom Index (DSI) [29]	SAQ	30 Questions regarding presence of specific symptoms, when present scored on a 5-point Likert scale. Used in Dutch nephrological care as PRO.	Yes/no, if yes 1 (‘not at all’) to 5 (‘very much’). Total score 0–30 for each ‘yes’, higher scores indicating higher number of symptoms. No cut-off values.
Costs	Five-level EQ-5D (EQ-5D-5L) [30]	SAQ	5 Questions regarding health aspects (mobility, self-care, usual activities, pain/discomfort, anxiety/depression) using a 5-point Likert scale and 1 overall health score on a visual-analogue scale. Used to calculate QALYs in cost-effectiveness analysis	1 (‘no problems’) to 5 (‘unable to/extreme problems’); 0 ‘worst health you can imagine’ to 100 (‘the best health you can imagine’ for the visual-analogue scale. Reference values using Dutch value set [31].
	(subset of questions from) iMTA Productivity & Medical Costs Questionnaire [32, 33]	SAQ	8 General questions and 22 questions on healthcare use in the previous 3 months. Used to calculate healthcare-related costs in cost-effectiveness analysis.	NA
Decisional regret	Treatment Choice Questionnaire & Decisional Conflict Scale (DCS) [34, 35]	SAQ	Questionnaire filled in when treatment choice has been made. Contains 23 questions regarding the choice made.	NA for Treatment Choice Questionnaire; 0–100 for DCS, higher scores indicating higher decisional conflict, no cut-off values.
	Decision Regret Scale (DRS) [36]	SAQ	5 Questions on regret regarding the choice for either conservative care or dialysis on a 5-point Likert scale.	0–25, higher scores indicating stronger feelings of regret. No cut-off or reference values [37].

*Abbreviations*: *CA* Clinician Assessment, *HRQoL* Health-Related Quality of Life, *IAQ* Interviewer-Administered Questionnaire, *iMTA* Institute for Medical Technology Assessment, *PRO* Patient Reported Outcome, *SAQ* Self-Administered Questionnaire, *T* Test, *NA* Not Applicable, *QALY* Quality Adjusted Life Year

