### Outcome variables

The primary outcome parameter is HRQoL (Table 2). DIALOGICA will assess three secondary outcome parameters: clinical outcomes, cost-effectiveness, and decisional regret. The clinical outcomes that will be assessed are mortality, hospitalisation, functional status, cognitive functioning, and frailty. All outcomes are assessed with (repeated) measures during the first year of the second stage.

**Table 2 Tab2:** Study outcomes

Outcomes			Instruments
Primary outcome	HRQoL		SF-12 physical and mental component scores [28]
Secondary outcomes	Clinical outcomes	Mortality (all-cause)	ERA-EDTA codes [16, 47]
		Hospitalisation (all-cause)	ICD-10 codes [48]
		Functional status	Katz-ADL [14], Lawton-iADL [15]
		Cognitive functioning	MoCA [17], 6-CIT [18], LDST [20]
		Frailty	Clinical Frailty Scale [25]
	Cost-effectiveness		ICERs, calculated using EQ-5D-5 L [30] and iPCQ/iMCQ [32, 33]
	Decisional regret		Decisional Regret Scale [36]

All outcomes are repeated measures during the first year of the second stage (Fig. 1)

*Abbreviations*: *6-CIT* six-item Cognitive Impairment Test, *EQ-5D-5L* Five-level EQ-5D, *ERA-EDTA* European Renal Association - European Dialysis & Transplant Organisation, *HRQoL* Health-Related Quality of Life, *(i) ADL* (Instrumental) Activities of Daily Living, *ICD-10* International Statistical Classification of Diseases, 10th edition, *ICER* Incremental Cost-Effectiveness Ratio, *iMCQ* iMTA Medical Costs Questionnaire, *iPCQ* iMTA Productivity Cost Questionnaire, *LDST* Letter-Digit Substitution Test, *MoCA* Montreal Cognitive Assessment, *QALY* Quality Adjusted Life Year, *SF-12* Twelve-item Short Form Health Survey

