#### Clinical outcomes

Mortality will be analysed as all-cause mortality within the first year of the second stage. The cause of death will also be categorised into seven categories, based on the United Kingdom Renal Registry, using ERA-EDTA codes (Table S2) [16, 47]. Hospitalisation will be analysed as all-cause hospitalisation within the first year of the second stage and each individual episode will be categorised into seven categories, using ICD-10 codes (Table S3) [48]. Functional status, cognitive functioning, and frailty will be repeated measures (at the start of the second stage and after 12 months) using their respective instruments, described in the previous paragraphs.

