#### Cost-effectiveness

QALYs will be calculated using the EQ-5D-5L [30]. Total healthcare costs will be calculated using a subset of questions from the iPCQ and iMCQ [32, 33]. Cost-effectiveness will be assessed as total costs per QALY using incremental cost-effectiveness ratio’s (ICERs).

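### The only named cost source leaves months 6 to 9 and the time from the last form to death outside every recall window

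*Protocol article*

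**What the plan says.** Four statements in the protocol article together fix how first-year costs are collected.

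- **Recall.** Table 1 (Costs) describes the cost form as self-administered, with "22 questions on healthcare use in the previous 3 months". The Nephrogeriatric assessment section adds that "Nine questionnaires are answered independently by the patient at home".
- **Timing.** The same section says "Upon entering the second stage, a new NGA will be performed, repeated again at yearly intervals", and "The questionnaires on HRQoL, symptoms and costs are also repeated after 3 and 6 months into the second stage". Data registration agrees: "data collection will be performed at start, after 3 months, 6 months, 12 months, and thereafter annually". There is no form at month 9.
- **Source.** Under Cost-effectiveness: "Total healthcare costs will be calculated using a subset of questions from the iPCQ and iMCQ". Table 2 names the same instruments. No other cost source is given.
- **Horizon.** Under Outcome variables: "All outcomes are assessed with (repeated) measures during the first year of the second stage".

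Two other data streams cover the same year but are not assigned to costing. Under Clinical outcomes, all first-year admissions are analysed and "each individual episode will be categorised into seven categories, using ICD-10 codes". Data registration plans linkage, with consent, to Renine, the Dutch registry of kidney replacement therapy. For missing data, Statistical analysis specifies multiple imputation by fully conditional specification.

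**The concern.** A total for the year needs resource use from the whole year, or a rule that turns partial coverage into a total. With the stated recall and schedule, the form does not ask about one quarter of the year, even if every patient returns every form. It also cannot be returned after death, so use between the last form and death goes unreported. Care shortly before death may be costly, and mortality is itself an outcome compared between the groups.

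The stated missing-data method does not close either gap. For months 6 to 9 the form yields no value for any patient, so an imputation model has nothing observed to learn from. For the time before death, it would borrow from patients who lived to return a form.

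At stake is the incremental cost, the numerator of the incremental cost-effectiveness ratio. This is a secondary outcome, but the Background uses the cost of dialysis to motivate the study.

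**Working it through.** The article states no cost total, so there is no figure of its own to reproduce here.

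**Inputs.** Recall 3 months (Table 1). Forms at 0, 3, 6 and 12 months (Nephrogeriatric assessment, Data registration). Dialysis cost about EUR 92,000 per patient-year and first-year mortality 18% after dialysis start at age 70 or older (Background). Neither figure is given for conservative care.

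**1. Coverage for a one-year survivor**

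| Form at month | Window (months) | Within first year? |
|---|---|---|
| 0 | −3 to 0 | no, before time zero |
| 3 | 0 to 3 | yes |
| 6 | 3 to 6 | yes |
| 12 | 9 to 12 | yes |

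Covered: 3 + 3 + 3 = 9 of 12 months (75%). Uncovered: months 6 to 9.

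**2. If the recorded windows are simply summed.** 92,000 × 3/12 = EUR 23,000 per surviving dialysis patient. Among survivors, a quarter of any constant monthly cost difference between the groups is lost as well.

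**3. Time from the last form to death.** For a death at month t the unreported time is t if t < 3, t − 3 if 3 ≤ t < 6, and t − 6 if 6 ≤ t < 12. With deaths spread evenly over the year, the mean is 0.25 × 1.5 + 0.25 × 1.5 + 0.5 × 3.0 = 2.25 months.

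With a constant hazard h = −ln(1 − m)/12 for first-year mortality m, the mean at m = 18% is 2.18 months.

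**4. Share of person-time alive outside every window.** Mean months alive in the year are m/h. At m = 18%, h = 0.01654 per month, so 0.18/0.01654 = 10.88 months.

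- Windows summed: (0.82 × 3 + 0.18 × 2.18)/10.88 = 2.85/10.88 = 26.2%.
- Months 6 to 9 filled for survivors: 0.18 × 2.18/10.88 = 0.393/10.88 = 3.6%. At 92,000/12 = EUR 7,667 per month this is about EUR 3,000 per dialysis patient.

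| Assumed first-year mortality | Mean unreported months per death | Uncovered, windows summed | Uncovered, months 6 to 9 filled |
|---|---|---|---|
| 10% | 2.21 | 25.7% | 1.9% |
| 18% | 2.18 | 26.2% | 3.6% |
| 30% | 2.13 | 27.1% | 6.3% |
| 40% | 2.08 | 28.0% | 8.9% |

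Interpolation therefore removes most of the gap. What remains lies entirely just before death and grows with mortality, so it differs between the groups if their mortality does.

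**The case against.** A reader might infer that use in months 6 to 9 and before death is never observed. That is true of the form but not of the study. Every admission in the first year is recorded, dialysis status is the study's main determinant, and Renine linkage is planned. The missing step is to assign these data to costing.

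A reader might also infer that total cost is understated and the incremental cost too small. The documents do not support this. It requires treating months 6 to 9 as zero, and nothing in the article says so. An interpolated or rescaled total could err in either direction, and an interpolation rule is the kind of detail that an article leaves to the full protocol or analysis plan. The sign of the pre-death loss is also unknown. If mortality is higher under conservative care, more of the lost costs may fall in that group, and dialysis minus conservative care would then look too large.

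Several narrower objections also stand:

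- The EUR 23,000 is a ceiling under simple summing. It prices the resource that depends least on patient recall.
- The 18% is a background figure, not a lower bound.
- Annual forms after month 12 do not feed the stated outcome, which is limited to the first year. The mention of discounting does not change that.
- Nothing says that the stage-start form would be counted in the first-year total.
- A sparse schedule with short recall is a fair compromise in patients aged 70 or older.

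The choice of source is not answered by these objections. Recall, schedule and source are all stated in the article, and together they do not supply the quantity named. An analysis plan can fill months 6 to 9 by assumption, but the form gives it no data on the time before death.

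**Conclusion.** The point holds as a weakness in the stated cost source. The form covers 9 of 12 months for survivors, and for patients who die it misses a mean of about 2.2 months before death. Summing the windows would understate a survivor's cost by about a quarter, at most about EUR 23,000 for a dialysis patient. With months 6 to 9 interpolated, about 3.6% of person-time alive stays uncovered (1.9% to 8.9% for mortality of 10% to 40%), and the resulting bias in incremental cost has no known direction.

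These sizes assume full response while alive, a constant hazard of death, and cost that accrues evenly at the article's dialysis figure. The mortality range is an assumption, because the article gives no mortality or cost for conservative care. If care before death costs more per month than average, the share of cost that is missed exceeds the share of person-time. The change is worth making, because better data for the largest items are already collected or linked.

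**What to change.** Amend the Cost-effectiveness section as follows:

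- Cost admissions from the per-episode hospitalisation data, with unit prices, over the whole first year of the second stage or up to death.
- Cost dialysis treatment in the same way, from study records and from Renine for consenting Dutch patients. For Belgian centres, which a Dutch registry does not cover, use study records.
- Use the iPCQ/iMCQ subset only for the remaining items, with months 6 to 9 interpolated between the 6- and 12-month forms.
- Use the form at the start of the second stage as a baseline covariate only.

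No extra visit or form is needed. The price is some additional costing work and interpolation error in the remaining items. Use of those items between the last form and death stays unrecorded and should be acknowledged as a limitation.

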#### Functional status

Functionality will be assessed by using four instruments. Firstly, the Activity of Daily Living Scale by Katz et al. assesses the patient’s ability to perform activities of daily living independently [14]. It ranks adequacy of performance regarding the six functions of bathing, dressing, toileting, transferring, continence, and feeding. Secondly, the Instrumental Activities of Daily Living Scale by Lawton et al. measures eight domains of more complex independent living skills, such as handling finances, medication, and driving [15]. Thirdly, hand grip strength will be measured using a Jamar handheld dynamometer. Lastly, patients’ fall risk will be assessed by both asking for fall frequency in the last year and their fear of falling, using a numeric rating scale.

#### Psychological status

Psychological status is assessed by using a total of five instruments, including three cognitive tests. The Montreal Cognitive Assessment scores different types of cognitive abilities, such as orientation, short-term memory, executive function, and visuospatial abilities [17]. The Six-item Cognitive Impairment Test is a fast and simple tool to screen for dementia, consisting of only six questions [18]. Finally, the Letter Digit Subtraction Test is a speed-dependent task that measures complex neuropsychological processes including visual scanning, mental flexibilities, sustained attention, psychomotor speed, and information processing [19].

Depression is assessed in two steps: first two case-finding questions (‘Whooley-questions’) are used, extended with the fifteen-item Geriatric Depression Scale if one or both of the two initial questions are positive [21, 22]. The Life Orientation Test - Revised is a ten-item measure of optimism versus pessimism [23, 24, 38].

#### Somatic status

Somatic status will be evaluated by using three instruments. Treating clinicians will use the Clinical Frailty Score, which grades patients from 1 (‘very fit’) to 9 (‘terminally ill’) [25]. Comorbidity will be assessed with the Charlson Comorbidity Index [26]. Finally, the surprise question, a screening tool in which caregivers answer the question “*Would you be surprised if this patient died within the next twelve months?*”, will be applied [39]. The Mini Nutritional Assessment - Short Form is used to assess the nutritional status of patients [27]. It is a well validated screening tool for the geriatric population consisting of 18 questions, categorising patients as ‘well-nourished’, ‘at risk of malnutrition’ or ‘malnourished’.

#### Social status

Relevant social data (e.g. marital and residential status, biographic data such as educational attainment, and support by home care professionals and/or caregivers) is registered.

#### HRQoL and symptoms

Patients’ HRQoL will be measured by the Twelve-item Short Form Health Survey (SF-12) [28]. Together with the Dialysis Symptom Index (DSI), it was selected as the patient reported outcome measures in Dutch nephrological care by the Dutch Kidney Patients Association, the Dutch Federation for Nephrology, Nefrovisie, and Leiden University Medical Center [29, 40]. The SF-12 and DSI were introduced for all Dutch patients on maintenance dialysis in 2018 [40]. The SF-12 consists of 12 questions regarding HRQoL and is the shorter version of the Short Form-36 (SF-36), the most widely used survey to assess HRQoL [28]. The SF-36 consists of eight domains: physical functioning, role-physical, bodily pain, general health, vitality, social function, role-emotional, and mental health. These domains are summarised in the Physical Component Summary Score and the Mental Component Summary Score. In the SF-12 these summary scores are calculated from the twelve most important items (explaining 90% variance) of the SF-36 questionnaire [41]. As the average difference in summary scores between SF-12 and SF-36 is quite small, for time-efficiency reasons, the SF-12 can be used reliably in cohort studies [42]. The DSI is a set of 30 questions evaluating the severity of symptoms in patients with kidney failure (Table S1) [29]. Patients report the level of burden of the symptoms on a five-point Likert scale, ranging from ‘not at all bothersome’ to ‘very bothersome’. Since these symptoms, such as nausea, energy loss, and shortness of breath, are common in patients with kidney failure and not specifically related to dialysis treatment, this questionnaire is also applicable to patients treated with CC.

